## Abstract

**Background:**

Childhood overweight and obesity is the most prevalent and, arguably, politically complex child health problem internationally. Governments, communities and industry have important roles to play, and are increasingly expected to deliver an evidence-informed system-wide prevention program. However, efforts are impeded by a lack of organisational access to and use of research evidence. This study aims to identify feasible, acceptable and ideally, effective knowledge translation (KT) strategies to increase evidence-informed decision-making in local governments, within the context of childhood obesity prevention as a national policy priority.

**Methods/Design:**

This paper describes the methods for KT4LG, a cluster randomised controlled trial which is exploratory in nature, given the limited evidence base and methodological advances. KT4LG aims to examine a program of KT strategies to increase the use of research evidence in informing public health decisions in local governments. KT4LG will also assess the feasibility and acceptability of the intervention. The intervention program comprises a facilitated program of evidence awareness, access to tailored research evidence, critical appraisal skills development, networking and evidence summaries and will be compared to provision of evidence summaries alone in the control program. 28 local governments were randomised to intervention or control, using computer generated numbers, stratified by budget tertile (high, medium or low). Questionnaires will be used to measure impact, costs, and outcomes, and key informant interviews will be used to examine processes, feasibility, and experiences. Policy tracer studies will be included to examine impact of intervention on policies within relevant government policy documents.

**Discussion:**

Knowledge translation intervention studies with a focus on public health and prevention are very few in number. Thus, this study will provide essential data on the experience of program implementation and evaluation of a system-integrated intervention program employed within the local government public health context. Standardised programs of system, organisational and individual KT strategies have not been described or rigorously evaluated. As such, the findings will make a significant contribution to understanding whether a facilitated program of KT strategies hold promise for facilitating evidence-informed public health decision making within complex multisectoral government organisations.

**Trial registration:**

Australia and New Zealand Clinical Trials Register (ANZCTR): ACTRN12609000953235

## Background

Obesity is a significant global public health issue. In Australia, a recent national health survey found 25% of children aged 5-17 years have been classified as overweight or obese. Childhood obesity has been linked to a range of social and physical health problems in later life including type 2 diabetes [1]. As a result, data suggests that the financial cost of obesity in 2008 was $8.283 Billion AUD [2]. Such forecasts are fuelling political imperatives to implement obesity prevention strategies, particularly for primary-school aged children. Developing strategies that incorporate new knowledge into policy development is essential.

Local governments in Australia have responsibility for a range of local infrastructure and activities including maternal and child health programs, child care, kindergartens, recreation facilities, parks, planning and building, traffic management and food regulations. Due to this diverse portfolio, local government has the potential to make a significant contribution to obesity prevention in Australia [3,4]. To be most effective however, strategies undertaken by local government need to be informed by the best available research evidence. Research evidence can be broadly defined as including descriptive evidence of prevalence and risk, evidence of intervention or program effectiveness and evidence about implementation of these interventions (for whom interventions work or not, in what circumstances and why) [5-7]. The crucial role of evidence has been formally acknowledged in this arena in Victoria with the Victorian Health and Wellbeing Act 2008, stipulating that local governments use evidence to inform their Municipal Public Health Plans [8]. The use of research evidence is important not only in terms of identifying the combinations of strategies that impact on obesity, but also how well they work, for which sub-groups, the potential for harm, the mechanisms needed to support strategies, and associated cost [9]. The use of research evidence to inform decision-making, and the development of strategies to support this process is therefore crucial.

Evidence-informed decision-making (EIDM) involves integrating the best available research evidence with contextual factors including community preferences, local health issues, political preferences and public health resources[10]. The benefits of EIDM include:

▪ adoption of effective and cost-efficient interventions,

▪ prudent use of scarce resources,

▪ improved client satisfaction, and

▪ better health outcomes for individuals and communities [10].

In order for evidence-informed decision-making to occur efficiently and effectively, a series of mechanisms are required. Researchers and decision-makers need to work in partnership to fund and conduct research that addresses key policy questions; research needs to be conceptualised, conducted and communicated in a way that is meaningful to decision-makers[11]; and research evidence needs to be accessed, assessed and appropriately [12] applied by decision-makers within a complex political system. (Appropriate use of research evidence to inform decision-making refers to an unbiased assessment of the evidence-base rather than using research evidence to support a position or decision that been made in the absence of evidence)

While decision-makers are under increasing pressure to use research evidence to inform their decisions, significant barriers have been identified. These include absence of personal contact between researchers and policy-makers and practitioners, lack of time and resources, organisational structures and processes, timeliness of research, poor quality or limited availability of research, and political influence [11-14]. To address these barriers, a range of strategies, often conceptualised as knowledge translation (KT) have been described and in some cases implemented. KT strategies range from researcher focused interventions (often designed to support the dissemination of research findings), decision-maker focused interventions (often designed to change practices and behaviours related to the integration of research evidence into decision-making processes) and interventions designed to create partnerships between researchers and decision-makers (where questions of mutual interest are identified, research is conducted in partnership and the research is used to inform policy-level decisions) [15]. These have also been categorised as interventions that encourage push, pull and exchange of evidence [16]. This study focuses on the application of decision-maker focused interventions, that is, those that facilitate decision-makers to access and use research evidence to inform their decisions.

Despite the fervour around KT in public health, very few rigorous studies have been or are being conducted [17]. As a result, it is likely that strategies have been either modified from those conducted in clinical environments or informed by the plethora of studies (of varying quality) that outline barriers and facilitators to KT in public health environments [16]. Much of the work to date has occurred in Canada where the government has actively invested in exploring and facilitating KT [18]. This exploratory trial will assess the potential effectiveness, as well as feasibility and acceptability, of a multi-component KT intervention in increasing the use of research evidence to support decision making in local governments. The trial is informed by a series of preliminary projects including a state-wide survey, a systematic review and key informant interviews, which will be published elsewhere. This paper describes the methods of the trial in detail.

## Aims and objectives

1. What KT strategies show promise to increase the use of research evidence in policy and program decision-making in local governments?

2. How can we measure evidence use and the key sub-components of evidence use (as outlined in Figure 1) that are to be targeted by the intervention, at decision-maker and council level?

**Figure 1 F1:**
[figure not shown]
**Proposed study timetable**.

3. What are estimates of intra-cluster correlation by council of outcomes and of the change in such outcomes that a larger trial would need to be powered to detect?

In order to answer these questions this research program has 2 key aims:

1. Undertake an exploratory cluster randomised controlled trial to identify acceptability of the multi-component knowledge translation and exchange model, identify potential modifications, estimate key parameters required for a full scale trial including recruitment procedures, recruitment and retention rates, variation in outcome measures, intra-cluster correlation coefficients, and estimate feasible effect sizes and intervention costs for a full scale trial.

2. Develop recommendations about KT models applicable to local government settings and specific recommendations for the value and design of a large scale trial.

## Methods/Design

### Study design

The study design is a cluster randomised controlled trial where local governments (councils) are randomised to intervention or control.

The intervention consists of two core components: 1. improved access to research evidence via provision of summaries of intervention research on topics of relevance in childhood obesity prevention for local government; and 2. building capacity of local governments to use research evidence to inform public health decision-making by providing facilitated support. Control (comparison) councils will receive component 1 and intervention councils will receive both components. The duration of the intervention will be two years. Figure 1 outlines the proposed study timetable.

#### Intervention councils

Facilitated support will be managed by a program coordinator and consist of:

▪ Increased access to research evidence through supplementing evidence summaries with support to assess applicability of evidence to local context,

▪ Professional development sessions with a focus on acquiring, assessing and applying research evidence to local context,

▪ Explore and implement strategies aimed at the development of an organisational culture that supports evidence-informed decision-making within local governments.

#### Comparison councils

The comparison councils will receive access to summaries of intervention research. These will be circulated by email to all participating councils.

This research program will incorporate two of the phases in the UK Medical Research Council's (MRC) framework for evaluating complex interventions: Phase I and Phase II [19]. The developmental research program involved development of the intervention's components, based on existing evidence, survey data and key informant interviews.

This paper reports on the design of the intervention trial, which is being conducted in 28 councils (14 randomised to participate in the intervention and 14 to act as comparison councils). This will inform the development of a case for a possible future Phase III trial [19].

Ethical approval for this project was granted by the University of Melbourne Human Ethics Committee [ref 0722362).

### Recruitment and randomisation of local governments

#### Baseline survey

All 79 Victorian local governments were invited to participate in a state-wide baseline survey. Individuals that were employed by Victorian local governments and involved in public health were eligible for participation. Up to four people from each local government were invited to complete an online survey. The survey aimed to elicit how local governments currently make decisions, the contribution of research evidence to decision-making, the facilitators and barriers to EIDM to identify strategies already in place that support evidence-informed decision-making and to explore additional strategies that might support EIDM. One hundred and thirty six responses from 45 local governments were received. Reasons for non-participation included workload, staffing issues (e.g. positions currently vacant), and a recent bushfire disaster. Many of those unable to participate said that they supported the study and asked to be kept informed of the outcomes. Only those local governments who agreed to participate in the initial survey were invited to participate in the trial.

#### Intervention study

All 45 councils who completed the pre-trial baseline survey were then invited to participate in the trial. Contact was made initially by phone and then a memorandum of understanding (MOU) was emailed for the key contact to complete. The MOU articulated the roles and responsibilities of both councils and researchers. Members of the research team were available to answer queries, either by telephone or site visit during the recruitment stage. Follow-up telephone calls were made to unresponsive key contacts. Councils who declined participation were removed from the sample and not contacted again for recruitment purposes.

#### Randomisation

Stratified block randomisation was used to randomly allocate participating councils to intervention or comparison group. Strata were defined by tertile of council's annual budget. Analysis of the baseline survey revealed a linear relationship between budget and population size which suggested that either could be selected as the stratification variables. Given the anticipated resource implications of practicing EIDM (e.g. staffing resources, access to internet and other resources), council budget was deemed to be most appropriate. Each intervention council then nominated a number of staff to participate in the intervention, ideally those who participate in public health planning. Once participation was agreed and a memorandum of understanding was signed, the programme coordinator emailed the trial manager with the name and annual budget of the council. The trial manager then emailed the trial statistician with the stratum (but not name) of the council. The statistician then allocated the council (blind to its identity) to intervention or comparison on the basis of a randomisation sequence of block size 4 generated and held by the trial statistician and concealed to all other parties. The trial manager logged the group allocation on the trial database and informed the program coordinator.

### Sample size

Given that the outcome measures had not previously been employed precise sample size calculations, whilst broadly estimated a priori, were unable to be undertaken in the absence of estimates of standard deviation and intra-cluster correlation. However, this study will provide estimates of SD and ICC.

### Outcome measures

#### Primary outcome measures

1. Research evidence use by LGs in intervention and comparison councils

#### Secondary outcome measures

1. Access to research evidence

2. Confidence using research evidence

3. Organisational culture for evidence-informed decision-making

4. Influence of research evidence on public health decisions

5. Usefulness of research evidence in making public health decisions

### Measurement of outcomes

Outcome evaluation will include the EIDM survey and a series of policy tracer studies. Outcome evaluation will focus on research evidence generally and research evidence specific to obesity prevention.

### EIDM survey and key informant interviews

Following the intervention period, all participants will be invited to complete an on-line survey. This will include those who have actively participated in the intervention components as well as representatives nominated from comparison councils. Unresponsive participants will be contacted once with an email reminder. A purposive sample of participants in both comparison and intervention groups will also be invited to participate in key informant interviews.

The post intervention survey will comprise measures developed in the analysis of the baseline survey as outcome measures, testing the sensitivity of the measures and aiming to obtain estimates of standard deviation and intra class correlation. Outcome measures will include access, confidence, and organisational culture in addition to the perceived influence and usefulness of a range of sources of evidence. Given the complexities associated with measuring research use, a triangulated approach to measuring a range of constructs of research use will be used.

The background and development of the EIDM survey and results of the baseline survey will be published separately, however in summary it was based on two measurement tools [20,21], the first previously assessed for reliability and validity amongst public health decision-makers in Canada [22], and the second developed for use with public health decision-makers working in local authorities in the UK [20]. These measures were modified to be relevant for use in local government in Victoria, based on related literature [22-25]. The EIDM questionnaire was pilot tested with five individuals who had either worked with or in local government.

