### Data management and analysis

Quantitative data will be collected using the EIDM survey. Participant responses will be collected using Survey Monkey [29] and then transferred to Stata for analysis [30].Baseline characteristics of intervention and comparison councils and staff will be compared. Summary statistics for each outcome, broken down by group, will be presented at follow-up, with 95% confidence intervals appropriately adjusted for clustering (Stata svy procedures).

The primary analysis for assessment of the effect of KT4LG on primary outcomes would be ascertained in a large scale trial using a council-level weighted regression model with the stratification variable (budget tertile) and baseline measures included as covariates, It is acknowledged that the sample size in this exploratory trial is small and therefore provide imprecise effect estimates (and 95% confidence intervals). More usefully, the data from this study will be analysed to provide estimates of the intracluster correlation for each outcome, which will be calculated using analysis of variance (Stata loneway), and of standard deviations and correlations of baseline and follow up measures (council and staff level).

Qualitative data will be collected in a variety of ways but will predominantly involve key informant interviews and process diaries maintained by the KB. Key informant interviews will be tape-recorded and transcribed verbatim. Given the lack of one theoretical approach to guide this work, a grounded theory approach will be used to inform qualitative data analysis [31-33]. The qualitative data will be coded and categorised using N-Vivo software [34] to identify emerging patterns and themes. While this study seeks to influence the use of research evidence it is acknowledged that other types of knowledge also inform decision-making. The process evaluation will collect this information and will also explore the influences on decision-makers [35].

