## Discussion

This study will make a significant contribution to better understanding how to support evidence-informed policy and practice decisions in local public health environments. This is important given the increasing pressure for policy makers to use evidence to inform their decision-making processes. As one of few rigorous evaluations in this area, it will build on a limited body of knowledge relevant to public health.

The study uses a rigorous design to explore an area that is complex and not well understood. There is likely to be considerable heterogeneity between local governments. In addition, there is likely to be staff turnover within councils as the intervention is implemented. These issues have been addressed in the study design.

Identification of outcome measures to assess the effectiveness of KT will be informed by the literature and from findings from Dobbin's Canadian study [22]. Further research on relevant outcome measures is needed and the research team intends to secure additional funding in this area.

This intervention, designed to support evidence-informed decision-making, is timely and relevant to the current context in which policy decisions are being made. The intervention will contribute to better understanding how evidence can be is used to informed public health decisions, what the barriers are, and identify at what level interventions are needed to support transparent and well informed decisions.

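### Follow-up respondents are described by participation in one arm and by nomination in the other, so the arms can differ through selection with no intervention effect

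*Protocol article*

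**What the plan says.** The section on the EIDM survey and key informant interviews opens broadly: "Following the intervention period, all participants will be invited to complete an on-line survey". It then describes who that covers: "This will include those who have actively participated in the intervention components as well as representatives nominated from comparison councils". No criterion or date is given for the nomination in comparison councils.

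The Randomisation section explains how intervention staff are found: "Each intervention council then nominated a number of staff to participate in the intervention, ideally those who participate in public health planning". Allocation itself works on the council. Once the memorandum is signed, "the programme coordinator emailed the trial manager with the name and annual budget of the council", and only the stratum goes on to the statistician. No list of staff is described at that stage. The split is "14 randomised to participate in the intervention and 14 to act as comparison councils".

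The baseline survey came before the trial and used one rule for every council, namely staff involved in public health: "Up to four people from each local government were invited to complete an online survey".

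Under Data management and analysis, the effect model is a weighted council-level regression with budget tertile and baseline measures as covariates. The data are also to yield intracluster correlations and "standard deviations and correlations of baseline and follow up measures (council and staff level").

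The Discussion expects heterogeneity between councils and turnover of staff, and adds: "These issues have been addressed in the study design".

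**The concern.** Randomising councils balances the councils. It does not balance the people who answer for them if those people are picked differently in each arm. Staff who join and stay with a programme on using research evidence may already score higher on access, confidence, culture and perceived influence of evidence. All of these are self-reported. If such staff answer for one arm and a differently chosen set answers for the other, a difference can appear without any effect of the programme.

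The aims make feasible effect sizes a product of this trial, for use in planning a full-scale one. The protocol admits that its effect estimates will be imprecise. Imprecision shows in the width of a confidence interval; a selection shift does not, and it would pass unseen into the next trial's assumptions.

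**Working it through.** **Step 1. The sampling rules side by side.**

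- Baseline, all councils: up to four people involved in public health, invited before allocation. The rule is the same everywhere.
- Follow-up, intervention councils: staff nominated by councils already known to be in that arm, described as active participants.
- Follow-up, comparison councils: nominated representatives, with criterion and timing not stated.

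The two follow-up rules differ from each other, and neither is tied to the baseline rule. Nothing makes the follow-up respondents the same people as at baseline, and turnover is expected. A council's baseline mean may therefore come from a differently chosen set of staff, so adjusting for it may not remove a selection shift. The staff-level correlation can be computed only where one person answered twice.

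**Step 2. Inputs for an illustration.** The protocol gives no SD, ICC, power or effect size, so there is no figure of its own to reproduce.

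- From the protocol: 14 councils per arm (14 + 14 = 28); baseline replies per council 136/45 = 3.02, taken as m = 3.
- Assumed: ICC 0.10, equal cluster sizes, an unadjusted comparison of council means with 26 degrees of freedom, two-sided 5%.

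**Step 3. Standard error of the arm difference, in SD units.**

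SE = sqrt(2 × (1 + (m − 1) × ICC) / (14 × m)) = sqrt(2 × (1 + 2 × 0.10) / 42) = sqrt(2.4/42) = 0.239.

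For ICC 0.01 to 0.20 the SE runs from 0.22 to 0.26.

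**Step 4. Consequence of a selection shift b when the intervention does nothing.** The estimate is biased by b. The rejection probability comes from a noncentral t with noncentrality b/0.239. One minus that probability is the coverage of a nominal 95% interval.

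| Shift b (SD) | Rejection at nominal 5% | Coverage of nominal 95% interval |
|---|---|---|
| 0 | 5% | 95% |
| 0.1 | 6.9% | 93.1% |
| 0.2 | 12.7% | 87.3% |
| 0.3 | 22.7% | 77.3% |
| 0.5 | 52.2% | 47.8% |

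**Step 5. What shift is plausible?** Suppose a share f of eligible staff is active and is surveyed in the intervention arm, an unselected set is surveyed in the comparison arm, and engagement correlates r with the outcome. Then b = r × φ(z)/f, where z is the (1 − f) normal quantile. For f = 0.5, φ(0)/0.5 = 0.798.

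| f | b at r = 0.1 | b at r = 0.5 |
|---|---|---|
| 0.8 | 0.035 SD | 0.175 SD |
| 0.5 | 0.08 SD | 0.40 SD |
| 0.4 | 0.10 SD | 0.48 SD |

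A simulation of 20,000 replicates took the most engaged 3 of 6 staff against a random 3 of 6, with ICC 0.05. It gave 0.07 SD at r = 0.1, 0.21 SD at r = 0.3 and 0.34 SD at r = 0.5, with rejection rates of 6.2%, 14.5% and 30.9%. With r = 0 it gave 0.00 SD and 5.0%. Both f and r are assumptions. The range runs from negligible to serious, and the documents do not say where the trial lies in it.

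**The case against.** The strongest reply is that the protocol invites all participants and only says that this includes the active ones. A reader might infer that inactive nominees are shut out and that the comparison is not by intention to treat. The text does not say so; such nominees are not excluded. What stands is narrower: even with them included, intervention respondents were chosen after allocation to join a programme, and comparison respondents were not.

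A reader might also infer that comparison staff were nominated after allocation. That is likely, since a council becomes a comparison council only then and no earlier list is described, but the article gives no date.

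Nor is the direction shown. Comparison councils may nominate their keenest contact, and the planning role that intervention councils were to look for is close to baseline eligibility. A shift favouring the intervention is plausible, not established.

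The trial is exploratory and places its effect model in a future large trial, so the rejection rates above attach to no decision here. That objection holds for the test and lowers the severity. It does not dispose of the bias, because effect estimates with intervals are still expected and are meant to inform planning.

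It is tempting to add that the SDs and ICCs are distorted too. They may be, but nothing here measures that. The council-level model does not need linked individuals; only the staff-level correlation does.

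On turnover, the process evaluation will record it. Recording is useful, but the survey's sampling rule still does not deal with it.

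**Conclusion.** The point holds in this form: follow-up respondents are described by participation in one arm and by nomination in the other, and this permits a selection difference that randomising councils does not prevent and council-level baseline adjustment may not remove. The direction is uncertain and the size unknown. Under the stated assumptions, a shift of 0.1 to 0.5 SD moves the estimate by the same amount, against a standard error of about 0.24 SD, and takes a nominal 5% test to about 7% to 52%. Those percentages only give a sense of scale, because no formal test is planned. Given the exploratory aim, this should be fixed rather than being a bar to proceeding.

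**What to change.** State one role-based rule for the follow-up survey in all 28 councils, independent of participation:

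- Invite the baseline-survey respondents plus the current holder of any eligible post since vacated, up to four per council (at most 28 × 4 = 112 people).
- Invite everyone on that list whether or not they took part, and analyse by allocated arm.
- Report active participants only as a secondary or process description, not as the between-arm comparison.
- Compute staff-level baseline to follow-up correlations only in people who answered both surveys, and say so.

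If baseline replies cannot be traced to individuals (the article does not say), list the eligible posts by role in each council instead. The staff-level correlation would then not be available.

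The cost is a changed invitation list, one protocol paragraph and a few more invitations. Some intervention respondents will have had little exposure, so the effect estimate will be somewhat diluted. The change has to come before the survey is sent, because analysis cannot recover staff who were never invited.
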